# HiSNAP trial—a multicentre, randomised, open-label, blinded end point, safety and efficacy trial of conventional (300 mg/kg) versus higher doses of acetylcysteine (450 mg/kg and 600 mg/kg) in patients with paracetamol overdose in the UK: study protocol

**DOI:** 10.1136/bmjopen-2024-097432

**Published:** 2025-03-22

**Keywords:** CLINICAL PHARMACOLOGY, Hepatology, Clinical Trial

## Abstract

**Introduction:**

In overdose, a larger proportion of paracetamol (acetaminophen) is converted in the liver to the toxic metabolite *N*-acetyl-*p*-benzoquinone imine (NAPQI). Glutathione (GSH) is the endogenous antioxidant that protects cells from NAPQI-induced injury. In overdose, GSH stores may become depleted, leaving NAPQI free to produce liver damage. *N*-Acetylcysteine (NAC) helps prevent paracetamol toxicity by replenishing liver GSH. This protective effect of NAC produces specific metabolites in the circulation. Currently, regardless of the paracetamol dose ingested, patients in the UK receive a dose of NAC based only on their weight. Basic pharmacology, mathematical modelling and observational studies suggest that this dose may be insufficient in some patients (particularly those taking a large overdose).

**Methods and analysis:**

A multicentre trial, taking place across several hospitals in Scotland, UK, within Emergency Departments and Acute Medical Units. Recruitment commenced on 19 February 2024 and is anticipated to run for approximately 2 years. This is a three-group dose-finding trial, in which participants are assigned in a 1:1:1 ratio to either Standard NAC (300 mg/kg) or higher doses of 450 mg/kg (Group 1) and 600 mg/kg (Group 2). The primary outcome is the proportion of paracetamol metabolites in the circulation that are directly produced by GSH/NAC detoxification of NAPQI. A higher proportion of these metabolites will indicate that the additional NAC is reducing the amount of toxic paracetamol metabolites in the body. The study will first test the primary outcome on the HiSNAP Group 2 against Standard NAC; only if that is significant will HiSNAP Group 1 be tested against Standard NAC.

**Ethics and dissemination:**

The HiSNAP trial has been approved by the East Midlands (Derby) Research Ethics Committee (reference 23/EM/0129), NHS Lothian Research and Development Department, and the MHRA. Results will be disseminated by peer-reviewed publication, conferences and linked on isrctn.com.

**Trial registration number:**

ISRCTN17516192.

STRENGTHS AND LIMITATIONS OF THIS STUDYThe study will systematically collect data to assess the safety and efficacy of higher acetylcysteine doses and the current standard dose.The study primary end point is measurable in every patient, in contrast to paracetamol overdose trials examining liver injury (which only occurs in approximately 10% of patients).The study has pragmatic inclusion criteria—the decision that the patient requires acetylcysteine lies with the clinical team.The study seeks to minimise imbalances between treatment groups by stratifying randomisation according to whether a patient is at high risk of liver injury after overdose.The study is limited by the primary outcome being biomarker-based. Any benefits on clinical outcomes will still require confirmation.

## Introduction

### Background

 Paracetamol (acetaminophen (APAP)) overdose is a common medical emergency. Across the UK, approximately 100 000 people attend hospital following a paracetamol (APAP) overdose every year (one every 5 min, same as myocardial infarction) and around half need admission for treatment with the antidote acetylcysteine (*N*-acetylcysteine (NAC)).^1 2^ Around 10% of these patients develop liver injury, and approximately three people die from paracetamol-induced liver failure every week.^3^ Paracetamol overdose is more common in Scotland than in any other UK region, or indeed globally.

### Rationale for the study

There is a lack of robust evidence to guide treatment decisions. The Cochrane Library published a systematic review of interventions for paracetamol overdose in 2018.^4^ The conclusion begins by saying, “These results highlight the paucity of randomised clinical trials comparing different interventions for paracetamol overdose and their routes of administration and the low or very low level quality of the evidence that is available.” This situation has resulted in differences in treatment protocols that are not evidence-based and do not have adequate safety assessments. High-dose NAC and repurposed, expensive drugs are being recommended for off-label use, yet no randomised controlled trials (RCTs) have been performed for these treatment recommendations.^5^ Novel therapeutics are now being developed for APAP overdose, and there is an expectation they will be subject to robust clinical trials prior to clinical use.^6 7^

Paracetamol is converted in the liver to the toxic metabolite *N*-acetyl-*p*-benzoquinone imine (NAPQI; figure 1). Glutathione (GSH) is the endogenous antioxidant that protects cells from NAPQI-induced injury. In overdose, GSH stores are depleted, leaving NAPQI free to produce liver damage. NAC prevents paracetamol toxicity by replenishing liver GSH. This protective effect of NAC produces specific metabolites in the circulation, as shown in figure 1. Currently, patients in the UK receive a dose of NAC that is based only on their weight. It is clear from the basic pharmacology, mathematical modelling and observational studies that some patients (particularly those taking a large overdose) may not be receiving enough NAC.^8^,^11^

**Figure 1 F1:**
[figure not shown]
Acetaminophen (APAP, paracetamol) metabolites. The study team has validated assays for APAP, APAP-Glu, APAP-Sul, APAP-GSH, APAP-Mer and APAP-Cys.^17^ NAPQI, *N*-acetyl-*p*-benzoquinone imine.

In the 1970s, a 20.25-hour regimen for delivering NAC was developed in Edinburgh and elsewhere that became the worldwide standard of care.^12^ The dose administered to patients using this regimen is limited by side effects that are directly related to the high initial rate of the NAC intravenous infusion. We designed, trialled and implemented a new regimen for NAC (the ‘SNAP’ regimen) that delivers the same total dose as the 21-hour regimen (300 mg/kg) but with fewer dose-limiting side effects while being quicker to complete (12 hours instead of 21 hours).^13^,^15^ This reduction in side effects means we can now safely test the effectiveness of higher doses. The SNAP regimen is endorsed by the UK National Poisons Information Service (NPIS) and the UK Royal College of Emergency Medicine and is now standard care across the UK and is used worldwide.^16^ Some patients treated with the SNAP regimen require an additional infusion after 12 hours and receive a higher dose of 500 mg/kg over 22 hours. It is therefore timely to investigate the effectiveness of higher doses of NAC as current evidence is inconclusive.^15^

### Objectives

In this trial, we will test the hypothesis that a higher NAC dose will increase detoxification of paracetamol. There are observational studies that suggest higher doses of NAC have the potential to reduce liver injury in patients taking large overdoses, but no RCTs have been performed and safety has not been rigorously assessed.^17^

### Trial design

To assess the risk/benefit profile of high-dose NAC, we propose a three-group dose-finding trial as shown in figure 2. The maximum dose to be studied is 600 mg/kg, chosen because mathematical models predict this will be a sufficient dose to effectively treat 98% of patients.^9^ The other treatment groups will receive 450 mg/kg (1.5× standard care) or 300 mg/kg (standard care). The primary outcome is the proportion of paracetamol metabolites in the circulation that are directly produced by GSH/NAC detoxification of NAPQI (ie, serum %GSH metabolite concentration after 12 hours of NAC). A higher proportion of these metabolites will indicate that the additional NAC is reducing the amount of toxic paracetamol metabolites in the body. For secondary end points, standard and novel liver injury markers will be measured to explore the effect of higher NAC doses on preventing liver injury. Safety will be assessed by systematically recording adverse events (AEs).

**Figure 2 F2:**
[figure not shown]
Trial design flow chart. Participants are randomised in a 1:1:1 ratio, with the potential to extend the sample size by up to 20% (ie, maximum of 108 patients) if agreed by the Trial Steering Committee, sponsor and funder. NAC, *N*-acetylcysteine.

## Methods and analysis

### Study setting

This is a multicentre trial, taking place across several hospitals in Scotland, UK, within Emergency Departments and Acute Medical Units. Recruitment commenced on 19 February 2024 and is anticipated to run for approximately 2 years. Eligible patients who have provided written informed consent will receive 12 hours of study intervention and will be followed up for 7 days. Refer to figure 3 for a study visit flow diagram.

**Figure 3 F3:**
[figure not shown]
Study visit flow diagram. AMU, Acute Medical Units; ED, Emergency Departments; NAC, *N*-acetylcysteine.

### Patient and public involvement

A patient and public involvement group for Emergency Medicine Research (Sheffield, UK) reviewed and gave feedback on the study design which was actioned prior to grant application submission. In addition, a survey of patients presenting with acute overdose was performed to explore willingness to participate in clinical trials, which demonstrated no difference between this group and general medical patients.

### Eligibility criteria

#### Inclusion criteria

All of

Paracetamol overdose presenting to hospital within 24 hours of taking their last dose of paracetamol. All patterns of overdose (single, staggered overdoses and therapeutic excess); accidental or deliberate; paracetamol alone or mixtures of tablets are eligible.Patient deemed to need NAC treatment by the clinical team.Blood paracetamol concentration and alanine aminotransferase (ALT) results are available (clinical care bloods).Provision of informed consent.Adult (16 years old or above).

#### Exclusion criteria

Any of

Patients who do not have the capacity to consent.Patients who are pregnant or breastfeeding.Patients who have previously participated in the study.Patients who, in the opinion of the responsible clinician/nurse, are unlikely to complete the full course of NAC, for example, expressing a wish to self-discharge.Patients detained under the Mental Health Act.Patients already started on NAC treatment.Patients with known viral hepatitis or HIV.Prisoners.

### Interventions

The product under investigation is NAC 200 mg/mL concentrate for solution for infusion, delivered by peripheral venous infusion per the SNAP regimen for the treatment of paracetamol poisoning. There will be three dosing groups:

Standard NAC as per the SNAP regimen (300 mg/kg): initial loading dose (100 mg/kg in 200 mL) given intravenously over 2 hours, followed by a second dose (200 mg/kg in 1000 mL) infused over 10 hours; *or*HiSNAP Group 1 (450 mg/kg): initial loading dose (150 mg/kg in 200 mL) given intravenously over 2 hours, followed by a second dose (300 mg/kg in 1000 mL) infused over 10 hours; *or*HiSNAP Group 2 (600 mg/kg): initial loading dose (200 mg/kg in 200 mL) given intravenously over 2 hours, followed by a second dose (400 mg/kg in 1000 mL) infused over 10 hours.

We will use the SNAP protocol for delivering NAC rather than the 21-hour protocol (as in the NAC marketing authorisation) because the SNAP regimen is the UK standard of care endorsed by the Royal College of Emergency Medicine and the NPIS.^16^ All hospital regions in Scotland use the SNAP regimen to deliver NAC treatment. The only variation to standard practice is that NAC doses will be calculated for each patient using their body weight to the nearest kilogram rather than a 10 kg weight-band as is currently used in clinical practice when patients receive Standard NAC (300 mg/kg). There is no placebo arm.

An H1 antihistamine (chlorphenamine 10 mg intravenous) and nebulised salbutamol may be administered to treat anaphylactoid reactions to NAC. Anti-emetic medicines may be given to treat nausea secondary to NAC. Any medication (prescription as well as over-the-counter drugs) or therapeutic intervention deemed necessary for the patient, and which, in the opinion of the investigator, do not interfere with the safety and efficacy evaluations, may be continued.

### Outcomes

#### Primary outcome

The primary outcome measure of efficacy is the proportion of paracetamol metabolites in the circulation that are directly produced by GSH/NAC detoxification of NAPQI (ie, (APAPCys+APAPMer+APAPGSH)/(APAPCys+APAPMer+APAPGSH+APAPGlu+APAPSul+APAP). A higher proportion of these metabolites will indicate that the additional NAC is reducing the amount of toxic paracetamol metabolites in the body.

#### Secondary outcomes

A full paracetamol metabolite panel (APAP-Cys, APAP-Glu, APAP-Sul, APAP-GSH, APAP-Mer) in serum and urine measured at baseline for serum and urine, 12 hours after the start of NAC for serum, and in the total urine collected in the 12-hour trial period will be conducted. Standard (ALT) and novel liver injury markers (keratin-18, miR-122) will be measured to explore the effect of higher NAC doses on preventing liver damage.^18^ International normalised ratio will be measured as a marker of liver synthetic function.

Repeat hospital admission within 7 days, acute liver failure, transfer to the Scottish Liver Transplantation Unit, liver transplantation and death will be reported.

To determine whether there are more AEs with higher NAC doses, adverse reactions will be measured by a Likert scale on the following nine symptoms: nausea, feeling flushed, itchy skin, skin rash, chest pain, headache, feeling breathless, feeling wheezy and tongue/lip swelling. A free-text box is also available. This self-assessment questionnaire will be completed as a baseline and again 12 hours after starting NAC. The number of events and severity of reactions will be used to compare each dosing group.

Safety will be assessed by systematically recording AEs (see ‘Safety assessments’). Anaphylactoid reactions and cerebral oedema are adverse events of special interest (AESI). The symptoms questionnaire will be reviewed as soon as possible after completion and within 7 days of infusion if the questionnaire is available. Any clinically significant events identified by an appropriately delegated physician will be recorded/reported as AEs/serious AEs (SAEs). A clinically significant event is defined as one which requires treatment and/or is recorded in the medical records.

### Recruitment

#### Identification

Patient screening will be undertaken by the nurses of the Emergency Medicine Research Group of Edinburgh. Participant eligibility will be verified by a delegated clinical trial physician after written informed consent has been obtained. Confirmation of eligibility will be recorded within the participants’ medical records and the participant added to the screening log.

The need for NAC treatment will be determined by the blood paracetamol concentration and liver function tests (including ALT) which are measured as part of routine care. Results from routine blood samples taken between 4 hours and 24 hours after the last ingestion of paracetamol overdose may be used for this eligibility assessment.

Pregnancy testing will be carried out prior to randomisation if a potential participant is of childbearing potential and could be pregnant, and this will be recorded in the patient’s medical notes and the electronic case report form (eCRF). Childbearing potential is defined as fertile, following menarche and until becoming postmenopausal unless permanently sterile. Permanent sterilisation methods include hysterectomy, bilateral salpingectomy and bilateral oophorectomy. A postmenopausal state is defined as no menses without an alternative medical cause for 12 months for women over 50 years old and for 24 months for women under 50 years old. A high follicle-stimulating hormone (FSH) level in the postmenopausal range may be used to confirm a postmenopausal state in women not using hormonal contraception or hormonal replacement therapy. However, in the absence of 12 months of amenorrhoea, a single FSH measurement is insufficient.

#### Randomisation

Randomisation will be carried out using a web-based randomisation service (managed by the Edinburgh Clinical Trials Unit (ECTU)). Participants will be randomised by any appropriately delegated member of the trial team to Standard NAC (300 mg/kg), HiSNAP Group 1 (450 mg/kg) or HiSNAP Group 2 (600 mg/kg) in a 1:1:1 ratio and minimised according to whether a patient meets the criteria of being at high risk of liver injury after overdose. High risk is defined as a hospital presentation ALT activity greater than the upper limit of normal (defined as >50 U/L) or a blood paracetamol concentration over the 300 line on the nomogram (applies only to single-acute overdoses; figure 4). A random element will be included in the minimisation to maintain unpredictability.

**Figure 4 F4:**
[figure not shown]
Nomogram used in UK clinical practice to determine if treatment is required for paracetamol overdose (100 line) and line used for trial purposes to determine if single-acute overdoses are over the 300 line.

Once a patient is randomised, they will remain in the study and have all outcomes recorded regardless of compliance with study allocation, unless they specifically withdraw consent to have data stored.

#### Blinding

This is not applicable—the study is not blinded. The trial team members responsible for measuring the primary end point by mass spectrometry will be blinded to the treatment group of each sample.

#### Participant retention

As participation in the study does not extend significantly beyond the normal duration of treatment and 7-day follow-up is conducted using medical records, we do not anticipate significant issues with participant retention.

### Study assessments

#### Use of study data

##### Data collection

Data will be collected from consent until 7 days after randomisation. Data items to be collected and data collection points are described in table 1. The local research team as delegated will be responsible for data collection and recording this in the eCRF. Data will be collected by trained and delegated members of the research team.

**Table 1 T1:** Study assessments

	Screening	Baseline	Pretreatment	Treatment	Post-treatment	Follow-up
	Day 1	Day 1	Day 1(30 min before NAC)	Day 1(time 0)	Day 1 or 2(conclusion of 12-hour treatment)	Day 7
Screening	X					
Consent	X					
Eligibility	X					
Urine pregnancy test	X					
Routine clinical bloods	X				X*	
Randomisation	X†  X†					
Medical history		X				
Symptoms questionnaire (AEs)			X‡		X§	
AEs identified by research team		X  X				
Study specific blood			X¶		X**	
Study specific urine			X¶		X**	
12-hour urine collection (volume)				X [figure not shown] X**		
NAC treatment per allocation				X		
Collection of outcome data (medical records)						X††

* Routine bloods (±1 hour) routine clinical bloods—if bloods (or individual parameters) are not requested by the clinical team, this will not be recorded as a deviation. If a routine sample is not available, the research team may take an additional sample to measure the end point parameters.

† Randomisation may take place at any time after consent but before NAC treatment depending on the availability of blood results.

‡ Baseline symptoms questionnaire 0–30 min before NAC treatment begins.

§ 5.12-hour symptoms questionnaire (±2 hours). Should ideally be collected as soon as possible after NAC treatment is completed. If participant is discharged before questionnaire us completed, the research team will make no more than three attempts to phone the patient and request the information retrospectively.

¶ Pretreatment interventions 30 min (±15 min).

** 12-hour study-specific samples (±2 hours). Should ideally be collected as soon as possible after 12-hour NAC treatment is completed. If participant refuses blood or urine sample collection, this will not be recorded as a deviation but will be captured in eCRF. Urine: the participant will be asked to empty bladder at 12-hour time point, so final volume can be recorded on eCRF and research sample collected. Blood: where a study-specific blood sample cannot be obtained, the research team will attempt to collect a sample from surplus clinical blood.

†† 7-day follow-up (+ 7 days). As day 7 follow-up is collected from the medical records; it can be reviewed and recorded in the eCRF up to 7 days after the time point, so it captures all relevant information.

AE, adverse events; eCRFelectronic case report formNAC, *N*-acetylcysteine

##### Data management

Data collected about the participants will be entered into a password-protected, secure database (REDCap; http://www.project-redcap.org) provided and maintained by ECTU.^19 20^ Trained and delegated members of the study team will be given password-protected logins to the database to complete data entry. No directly identifiable information will be entered into the electronic trial database.

Authorised personnel will be given protected access to relevant data. Consent is given from the participant. Examples of this include the Study Statistician in order to produce progress reports to the independent Data Monitoring Committee (DMC) and/or the interim or final statistical analyses; and the Trial Manager to produce blinded logistics reports; the Data Management Team to check the quality of the data and the QA manager for audit and ongoing quality assurance reports; as well as representatives of the sponsor for purposes of audit and monitoring or the regulatory authorities.

##### Data monitoring

The DMC will meet at least once each year or once 10 patients have been recruited into each trial arm, and subsequently when 20 patients have been recruited to each arm. The committee is an independent, multidisciplinary group with experience in the management of patients with paracetamol overdose, anticipated AEs and the conduct and monitoring of randomised clinical trials. Additional urgent meetings may be arranged if any cases of cerebral oedema occur.

### Sample size and analysis plan

We have profiled paracetamol metabolites using samples from the SNAP and MAPP trials (%GSH mean 2.16% (SD 1.81)).^17^ External validity is provided by a recent Australian cohort study that reported similar mean and SD for these metabolites.^21^ To detect a 45% difference in this toxicokinetic marker between standard and each of the HiSNAP groups (cf 50% effect size estimated from mouse pilot data), 30 patients per group will give a power of 88% (log-transformation of data, 5% two-sided significance level, analysis by analysis of covariance adjusting for baseline value, assuming correlation 0.62 between baseline and post-NAC %GSH). To control the overall type I error at 5%, we will incorporate a hierarchical hypothesis testing structure. We will first test the primary outcome on the HiSNAP Group 2 against Standard NAC; only if that is significant will we test HiSNAP Group 1 against Standard NAC. Patients with liver injury (and by definition, excessive NAPQI production) have an increase in metabolites of between double to fourfold (200–400%). Therefore, our study is powered to detect a clinically relevant effect size (45%).

The log-transformed primary outcome, %GSH metabolites, will be analysed using a normal linear model, adjusting for the pre-NAC %GSH value and for the continuous form of the baseline variables ALT and blood paracetamol concentration on which the minimisation factor is based. The treatment effect for each HiSNAP group versus Standard NAC will be estimated using the least-squares mean difference and its 95% CI, back-transformed to the original scale to give the ratio for HiSNAP:Standard NAC.

Continuous secondary outcomes will be analysed in the same way as the primary outcome. Categorical secondary outcomes will be analysed using logistic regression, adjusting for the minimisation variables in the same way as in the normal linear model and reporting the treatment effect in each HiSNAP group versus Standard NAC by OR (95% CI). A detailed statistical analysis plan will be finalised prior to database lock and unblinding of the trial statistician.

Exploratory predefined subgroup analyses will investigate the relationship between the treatment effect of each HiSNAP group and baseline levels of ALT and blood paracetamol level. Patients with a blood paracetamol concentration over 300 line on the nomogram are at a high risk of liver injury even with NAC treatment.^10^ This will be done separately for each baseline variable by including an interaction term with treatment group in the normal linear model for the primary outcome.

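### The stated 88% power is not reproduced by the inputs printed beside it; under a lognormal conversion they give about 70% for a ratio of 1.45

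*Protocol article*

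**What the plan says.** All the inputs are in the protocol article, section 'Sample size and analysis plan', unless noted.

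- Spread: metabolite profiling of samples from two previous trials is summarised as "GSH mean 2.16% (SD 1.81"), on the original scale. No log-scale SD is given.
- Effect: "To detect a 45% difference in this toxicokinetic marker between standard and each of the HiSNAP groups".
- Result and test: "30 patients per group will give a power of 88% (log-transformation of data, 5% two-sided significance level").
- Model: analysis of covariance on the baseline value, "assuming correlation 0.62 between baseline and post-NAC %GSH".
- Direction: under 'Objectives', "we will test the hypothesis that a higher NAC dose will increase detoxification of paracetamol".
- Effect measure: the log-scale difference is "back-transformed to the original scale to give the ratio for HiSNAP:Standard NAC".

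Testing is hierarchical: Group 2 against Standard NAC first, then Group 1 only if the first test is significant. The section concludes that the study has adequate power for a clinically relevant effect of 45%.

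**The concern.** The power and its ingredients stand in the same paragraph, so a reader should be able to get from one to the other. The natural route is a lognormal conversion, because the outcome is to be log-transformed, and it falls 17 to 18 percentage points short.

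The figure matters because the claim to be powered for a 45% effect rests on it. If the lognormal conversion is right, the first test in the hierarchy has about a 30% chance of missing a ratio of 1.45, not 12%, and a miss also closes off the test of Group 1. A non-significant result would then be weaker evidence against a 45% effect than the protocol suggests.

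**Working it through.** **Inputs.** Mean 2.16, SD 1.81, correlation 0.62, 30 per group, two-sided 5%, as printed. The 45% difference is read as a ratio of 1.45, because the hypothesis is an increase and the effect is reported as HiSNAP:Standard.

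**Assumption.** %GSH is lognormal. This is needed because the log SD is not printed.

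**Attempt to reproduce 88%.**

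1. CV = 1.81/2.16 = 0.838.
2. Log SD = √ln(1 + 0.838²) = √0.532 = 0.729.
3. Residual SD after ANCOVA = 0.729 × √(1 − 0.62²) = 0.729 × 0.785 = 0.572.
4. SE of the difference = 0.572 × √(2/30) = 0.148.
5. Effect = ln(1.45) = 0.372; effect/SE = 2.51.
6. Power = 69.6% (noncentral t, 57 df) or 71.1% (normal). A simulation of the ANCOVA with 20,000 runs gave 68.5%.

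The 88% is not reproduced. With 36 per group, the 108-patient maximum in Figure 2, power is 77.5% (t) or 78.7% (normal).

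**What would give 88% with 30 per group, changing one input at a time.**

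| Input changed | Noncentral t | Normal |
|---|---|---|
| Ratio | 1.60 | 1.59 |
| Log SD | 0.575 | 0.585 |
| Correlation | 0.79 | 0.78 |

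**Other readings of the text.**

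| Reading | Power (t) | Fits the text? |
|---|---|---|
| Original scale, ANCOVA | 74.1% | No: log-transformation is stated |
| 45% decrease, ANCOVA | 97.8% | No: an increase is hypothesised |
| 45% decrease, no baseline adjustment | 87.7% | No: wrong direction, and ANCOVA is stated |
| 0.45 as a log difference (ratio 1.57) | 84.9% (normal 86.1%) | No: not a 45% difference |
| Variance factor 1 − 0.62 | 88.2% (normal 89.3%) | Only if 0.62 is R-squared |

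For the last row, residual SD = 0.729 × √0.38 = 0.450, SE = 0.450 × √(2/30) = 0.116, and 0.372/0.116 = 3.2. The ANCOVA factor is 1 − r², so this is correct only if r² = 0.62, that is r = √0.62 = 0.79.

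**How far the result depends on shape.** Two alternatives keep mean 2.16 and SD 1.81.

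- Gamma: shape = 1/0.838² = 1.42, log SD 1.00, power 44%.
- Mixture: a lognormal majority with a fraction p of patients raised by a factor f. With M equal to f with probability p and 1 otherwise, log variance = ln[(1 + CV²)·E(M)²/E(M²)] + p(1 − p)(ln f)². For p = 0.10 and f = 4, E(M) = 1.3 and E(M²) = 2.5, so log variance = ln(1.702 × 1.69/2.5) + 0.09 × 1.922 = 0.140 + 0.173 = 0.313. Log SD is 0.56 and power 90%. For f = 2 or 3 with p = 0.10, log SD is 0.71 or 0.65 and power 72% or 80%. For p = 0.15 and f = 4, log SD is 0.584 and power 87% (t) or 88% (normal).

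The mixture takes its 10% from the article's liver injury rate and its two- to fourfold range from the sample size section; 15% is an assumption. All these figures treat 0.62 as the log-scale correlation and use the usual normal-theory power formula.

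**The case against.** The strongest defence is that a raw mean and SD do not determine a log SD. The team profiled the samples itself and planned on the log scale, so it may have taken the log SD directly from individual data. The mixture calculation shows that 88% is compatible with both printed moments if a minority of the source samples lay at the top of the stated range. This stands, and it is why 70% can only be a conditional figure. It does not rescue the statement as printed: the composition of the source samples is not shown, shape can move power down (gamma, 44%) as well as up, and no log SD near 0.575 appears anywhere in the article.

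A second defence is that the planned model also adjusts for ALT and paracetamol concentration, which could raise power. That may be so, but the power statement takes credit only for the baseline value.

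A reader might go further and infer that the trial's true power is 70%, or that an arithmetic error has been proved. Neither is supported. The missing log SD leaves the true power open, and the near-exact match at 88.2% points equally to a mislabelled parameter: if 0.62 is really R-squared, the 88% is sound and the word 'correlation' is wrong. If it is a correlation, a wrong variance factor is a plausible cause but not an established one. A reader might also deduct for refused 12-hour samples. Table 1 provides for surplus clinical blood when a study sample cannot be obtained, so the article gives no basis for a specific loss.

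**Conclusion.** The point holds as a mismatch between a stated result and its stated inputs. Taken at face value with a lognormal outcome, the inputs support about 70% power for a ratio of 1.45, against 88% stated. The 70% rests on the lognormal assumption, on 0.62 being a log-scale correlation, on 45% meaning a ratio of 1.45, and on 30 evaluable patients in each group. With the same printed moments, other shapes give about 44% to 90%, so 88% is not excluded; it is unsupported. Type I error control, the estimand and the planned analysis are unaffected.

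**What to change.** In the sample size section, and in the SAP if it repeats the calculation:

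1. State the log-scale SD used and where it came from.
2. State whether 0.62 is a correlation or R-squared, and on which scale it was estimated.
3. State that a 45% difference means a HiSNAP:Standard ratio of 1.45.
4. Recompute the power from these values.

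If the source data support a log SD near 0.575 or a correlation near 0.79, print that value and keep the 88%. If not, restate power as about 70% for a ratio of 1.45 and 88% for a ratio of about 1.60, with 30 evaluable per group under a lognormal assumption, and amend the sentence claiming power for a 45% effect.

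The cost is wording only; recruitment and analysis do not change. The price is that the stated power may become less favourable.

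### The 88% power stated for each HiSNAP group holds only for Group 2; through the testing hierarchy, Group 1 has about 80% if both groups have the 45% effect

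*Protocol article*

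**What the plan says.** The section Sample size and analysis plan of the Protocol article defines the target as follows: "To detect a 45% difference in this toxicokinetic marker between standard and each of the HiSNAP groups". For that target, "30 patients per group will give a power of 88"%, at a "5% two-sided significance level", on log-transformed data with covariance adjustment for baseline.

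The multiplicity rule follows directly: "To control the overall type I error at 5%, we will incorporate a hierarchical hypothesis testing structure". Group 2 is compared with Standard NAC first, and "only if that is significant will we test HiSNAP Group 1 against Standard NAC". The Methods and analysis part of the abstract repeats the rule: "only if that is significant will HiSNAP Group 1 be tested against Standard NAC".

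No second power figure is given for the conditional Group 1 test, and the 88% is not labelled as the power of one comparison taken alone. The paragraph ends by concluding that the study is powered for the 45% effect. The Randomisation section gives 1:1:1 allocation to the three groups.

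**The concern.** The wording attaches 88% to Group 1 as well as to Group 2. Yet Group 1's only confirmatory test takes place after a Group 2 success. Its power under the plan is therefore the probability that both tests reject, which must be lower than 88% unless Group 2 is almost certain to succeed.

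The Trial design section describes a three-group dose-finding trial, and 450 mg/kg versus Standard NAC is one of its two primary comparisons. A reader takes from the text that a true 45% effect at 450 mg/kg would be missed 12% of the time. With the same effect in both groups, the plan's rule makes that about 20%.

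**Working it through.** **Inputs from the Protocol article**
- Power 88%, 30 per group, two-sided 5%, 45% difference for each comparison (Sample size and analysis plan).
- Fixed sequence, Group 2 then Group 1 (same section).
- 1:1:1 allocation, one shared control arm (Randomisation).

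**Step 1: the plan's own 88%.** The section gives "GSH mean 2.16% (SD 1.81") on the raw scale and no log-scale SD. If the data are lognormal (an assumption), the log SD is √ln(1 + (1.81/2.16)²) = 0.729. With "assuming correlation 0.62 between baseline and post-NAC %GSH", the adjusted SD is 0.729 × √(1 − 0.62²) = 0.572. A 45% increase is ln 1.45 = 0.372. Then 0.372 / (0.572 × √(2/30)) − 1.960 ≈ 0.56, which is a power of 71.1% (normal approximation). Two other readings come close to 88%: a difference of 0.45 log units with baseline adjustment (86.1%), and a 45% reduction without the adjustment gain (88.8%). Because the log-scale SD is not stated, this remains a separate question. From here on, 88% is taken as given.

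**Step 2: noncentrality.** Power 88% at two-sided 5% requires 1.960 + 1.175 = 3.135. The chance of rejecting in the wrong direction is negligible.

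**Step 3: correlation of the two tests.** With equal group sizes n and residual variance σ², each difference from control has variance 2σ²/n. The two differences share the control mean, so their covariance is σ²/n. The correlation is (σ²/n) / (2σ²/n) = 0.5.

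**Step 4: Group 1 through the hierarchy, both effects 45%.**
P(Z2 > 1.960 and Z1 > 1.960), with both means 3.135 and correlation 0.5, is **0.802**.
- Simulation with a pooled-variance t test, each comparison set to 88%: 80.2% to 80.4%.
- Ignoring the shared control: 0.88 × 0.88 = 77.4%, so the correlation already helps the plan.

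**Step 5: a larger Group 2 effect, with Group 1 held at ratio 1.45.** The Group 2 noncentrality is 3.135 × ln(ratio) / ln 1.45. For a ratio of 1.5 this is 3.135 × 0.405 / 0.372 ≈ 3.42, which gives Group 2 a power of 92.8%.

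| Group 2 ratio | Power, Group 2 | Power, Group 1 through the hierarchy |
|---|---|---|
| 1.45 | 88.0% | 80.2% |
| 1.5 | 92.8% | 83.7% |
| 1.6 | 97.8% | 86.9% |
| 1.7 | 99.4% | 87.8% |
| 1.8 | 99.9% | 88.0% |

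**The case against.** The strongest reply is that 88% is the power of each pairwise comparison, a usual basis for sizing a multi-arm trial, and that the hierarchy is introduced afterwards for the sole purpose of controlling type I error. On that reading the figure is unlabelled rather than miscalculated. This stands in part: 88% is a coherent per-comparison figure, and the fault lies in applying it without qualification to a comparison that is never tested on its own.

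A second reply is that the plan does not say both doses have the same true effect. If the effect does not fall with dose, equal effects are the worst case for a Group 1 effect of 45%, and the sequence then costs between about 0 and 8 points. This also stands, so the 80% must carry its condition. It does not restore 88%, because the article names one 45% target for both groups and assumes no larger effect at 600 mg/kg.

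Stronger readings are tempting but not supported:
- *Group 1 power is only about a third, because a lower dose may have a smaller effect.* If Group 1 had half the log effect (an assumption), its power would be 34.7% before the sequence and 33.7% after it. Nearly all of that shortfall comes from an effect the plan never claims to detect; the sequence costs one point.
- *The sequence should be applied to a lower starting power than 88%.* That depends on the lognormal SD assumed in Step 1, which the document does not state.
- *The article needs a rule for interpreting an untested Group 1.* It already plans an estimate and 95% CI for each HiSNAP group versus Standard NAC. Anything further is detail for the analysis plan, which is not shown.

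**Conclusion.** The point holds as a correction to one power statement. Through the plan's testing rule, 88% applies to Group 2 only. For Group 1 it is about 80% if both groups have the 45% effect, a shortfall of about 8 points. The shortfall narrows to about 4 points at a Group 2 ratio of 1.5 and about 1 point at 1.6.

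This rests on taking the stated 88% as correct for a single comparison, on a correlation of 0.5 from equal allocation and a shared control, and on a Group 1 ratio of 1.45.

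A reader might infer that the hierarchy is flawed or the trial too small. The document supports neither: the fixed sequence is valid and controls the type I error at 5%, and nothing here changes the sample size or the analysis.

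**What to change.** In Sample size and analysis plan, replace the single figure with a statement to this effect:

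> Power is 88% for HiSNAP Group 2 versus Standard NAC. For HiSNAP Group 1 versus Standard NAC, tested through the hierarchy, it is about 80% if both groups have a 45% effect, and up to 88% if the Group 2 effect is larger.

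The cost is wording only. The number of patients, the order of testing and the model all stay as they are. The price is a less favourable published figure for Group 1.
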